## Abstract

**Background:**

Maternal and neonatal mortality remain elevated in low and middle income countries, and progress is slower than needed to achieve the Sustainable Development Goals. Existing strategies appear to be insufficient. One proposed alternative strategy, Service Delivery Redesign for Maternal and Neonatal Health (SDR), centers on strengthening higher level health facilities to provide rapid, definitive care in case of delivery and post-natal complications, and then promoting delivery in these hospitals, rather than in primary care facilities. However to date, SDR has not been piloted or evaluated.

**Methods:**

We will use a prospective, non-randomized stepped-wedge design to evaluate the effectiveness and implementation of Service Delivery Redesign for Maternal and Neonatal Health in Kakamega County, Kenya.

**Discussion:**

This protocol describes a hybrid effectiveness/implementation evaluation study with an adaptive design. The impact evaluation (“effectiveness”) study focuses on maternal and newborn health outcomes, and will be accompanied by an implementation evaluation focused on program reach, adoption, and fidelity.

**Supplementary Information:**

The online version contains supplementary material available at 10.1186/s12889-022-13578-y.

## Background

Maternal mortality is 40 times higher and neonatal mortality is 9 times higher in low-income countries than in high-income countries [1], the Millenium Development Goal target of reducing maternal mortality by 75% by 2015 was not achieved [2], and the current rate of maternal mortality reduction (-2.9% per year from 2000–2017) will need to more than double to achieve the Sustainable Development Goal (SDG) target [1].

Progress against neonatal mortality, which now accounts for 46% of all under-5 deaths, is similarly off track, with more than 60 countries unlikely to achieve the SDG target of a neonatal mortality rate of 12 per 1,000 births or lower by 2030 [3]. Current global strategies to reduce maternal and neonatal mortality in developing countries largely focus on extending the reach of decentralized, clinic-based antenatal and delivery care to populations that still lack access to this care [4]. A key element of this strategy has been to increase access to antenatal care and to increase the percentage of women who deliver in a health facility or with care from a skilled birth attendant. These indicators have improved rapidly in many countries. However, these increases have not resulted in commensurate reductions in maternal and neonatal mortality [1]. This suggests that access to basic care is not enough. Improving access to *high quality, definitive* maternal and newborn care is critical for reducing maternal mortality, neonatal mortality and stillbirths, reducing maternal and neonatal morbidity, and achieving SDG 3 targets.

One reason why quality remains inadequate for intrapartum care is that many facility deliveries take place in poorly equipped primary care clinics that do not consistently diagnose high-risk pregnancies, are not equipped to manage intrapartum complications, and do not have systems in place to consistently refer severe cases to hospitals in time [5]. Across a range of low and middle-income countries, quality of delivery care is better in higher-level facilities, while lower level facilities and low case volumes are often associated with low quality [6]. Recent evidence shows that in the absence of advanced care (such as well-equipped and staffed surgical theaters and newborn units), point-of-care quality interventions at primary care level are unlikely to save lives [7]. Other recent observational evidence shows limited effect on maternal or newborn mortality from low-level facility delivery in low income settings [8, 9].

The linked crises of maternal and early neonatal mortality, and the inadequacy of current strategies, highlight the need to accelerate progress by developing and testing new approaches to delivery and newborn care. The recent Lancet Global Health Commission on High Quality Health Systems [10] argued for a structural health system reform in high mortality settings with adequate geographic access to hospital care: shifting the default location for deliveries from primary care clinics to newly strengthened and expanded “delivery hub” hospitals equipped to provide caesarean sections, blood transfusions, focused care for sick newborns, and other advanced services. The proposed policy, known as “Service Delivery Redesign for Maternal and Newborn Health,” (SDR) envisions that prior to any shift in recommended delivery location, health system leaders would improve the quality of care available in delivery hubs, ensure adequate transportation options, strengthen networks of care between higher and lower-level facilities, and engage communities around the policy change. However, while there is increasing interest in the concept of SDR for maternal and newborn health, there is little rigorous evidence about the effectiveness of a shift to this proposed strategy in diverse low-income settings with scarce health system resources, a legacy of primary care delivery, and potential access challenges [11].

Kakamega County in western Kenya has decided to pilot a version of this policy: the county has begun to bolster, expand and equip “delivery hub” hospitals while improving emergency transportation access and granting facilities increasing scope to retain and manage locally-generated financial resources. After this period of system improvement focused on delivery care, the policy will be changed such that women will be strongly encouraged to deliver at nearby “delivery hub'' hospitals, rather than in primary care clinics (known as level 2 or level 3 health centers in Kenya). These interventions and policies represent a locally-adapted version of the SDR model. This protocol discusses the research design for a prospective study of the impact of SDR. The study comprises both an impact evaluation (“effectiveness”) component focused on maternal and newborn health outcomes, accompanied by an implementation evaluation focused on program reach, adoption, and fidelity.

## Methods

### Setting

Kakamega County is located in Kenya's Western Region, approximately 50 km from the Lake Victoria port of Kisumu. With a population of approximately 1.9 million, the county's maternal mortality rate was 316 per 100,000 live births and the neonatal mortality rate was 19 per 1,000 live births in 2014, when the most recent data is available [12]. There were approximately 70,000 births in the county in 2018; 35% of which occurred at home, 28% in primary care facilities (dispensaries (Level 2) and health centers (Level 3)) and 37% in hospitals (Level 4 and 5 facilities) [13]. There are 205 government health facilities in the county, 10 of which are Level 4 hospitals. Maternal and newborn care is free in most public health facilities throughout Kenya via the “Linda Mama'' program; additionally, Kakamega County introduced a conditional cash transfer program (“OparanyaCare'') for antenatal, delivery, postnatal care and immunizations to poor and vulnerable women.

### The intervention

SDR for maternal and newborn health is a multi-component health system reform. In Kakamega, SDR is being implemented by the County Department of Health, with support from the non-governmental organization (NGO) Jacaranda Health. Financing is from the County government and is supplemented by the Bill and Melinda Gates Foundation.

An initial feasibility assessment study examined the existing capacity, facility accessibility, political will and potential benefits of SDR in Kakamega County [13]. Based on this assessment, the County identified several components for a health system reform. First, it selected ten hospitals to serve as delivery hubs across the county. These were all public facilities; typically sub-county hospitals (level 4 hospitals in the Kenyan system). Before the intervention, the delivery hubs all conducted 1,000 or more deliveries per year, but not all had comprehensive emergency capabilities.

The first component of SDR is a preparation phase, in which delivery hubs are strengthened (Fig. 1) and prepared for the higher patient volumes that will result from the SDR policy change of encouraging delivery at delivery hubs. This includes deployment of additional staffing, as well as improvements to infrastructure and equipment. For example, designated delivery hub hospitals in Kakamega are scheduled to be staffed with additional nurses, doctors, and specialists: In addition to their pre-existing complement of medical officers, the current plan is for each delivery hub in Kakamega to have a surgeon, a pediatrician, an obstetrician-gynecologist, and a specialist medical officer posted to the facility to bolster delivery care.

**Fig. 1 Fig1:**
[figure not shown]
Service Delivery Redesign Theory of Change

On the infrastructure side, each delivery hub will have operating theaters built or improved, maternity wards expanded, and newborn units built or expanded. Facility capacity to deliver blood transfusions will also be augmented.

Delivery hubs are further from most women's homes than local clinics; traveling greater distances to deliver can be difficult, especially at night. In Kakamega's SDR reform, this issue will be addressed with the participation of the NGO Rescue.co, who contracts with private transport providers to provide emergency transport for pregnant women.

When delivery hubs are upgraded to a level that will enable higher patient volumes and improved quality of care, and complementary interventions such as emergency transport and facility financing reforms are in place, the government of Kakamega plans to communicate to all health workers, and all health system users, that policy regarding place of delivery has changed, and women are now expected to deliver at designated delivery hub hospitals. To this end, the last component of the intervention is this public communication element, which will be undertaken through media campaigns and public outreach meetings, as well as direct communication from health workers to antenatal care (ANC) clients.

### Research questions

#### Impact evaluation component

The main research question of the impact evaluation (effectiveness) component of this study is the impact of SDR in Kakamega County on maternal and newborn health, measured using a composite indicator of maternal and newborn health. The secondary research question examines the impact of SDR on patient satisfaction and perceived quality of care, maternal complications, out-of-pocket (OOP) expenditures, and utilization of care.

#### Implementation component

The main research objective for the implementation component of the evaluation will be to measure the implementation fidelity and reach, identify key obstacles to successful implementation as well as facilitating factors, and measure possible unintended consequences of SDR policy on health system functioning.

### Study design

This protocol describes two study designs for the impact evaluation component of the SDR evaluation: the first is a multi-phase stepped wedge design, for the planned situation in which SDR is progressively scaled up across all of Kakamega County’s sub-counties in three phases. However, due to the multi-year, complex nature of the SDR intervention, we also pre-specify a smaller scale, nested “phase 1'' study design which will be carried out for two reasons. First, a study based on phase 1 will be conducted to track a set of implementation indicators in order to assess policy implementation. As a pragmatic, real world health system evaluation, findings about implementation and take-up from this first phase can be used strengthen phase 2 and phase 3 implementation. Second, in the event that only the first phase of the reform is fully implemented, the full set of outcomes will be analyzed after phase 1 using a difference-in-difference design.

In the sections below we first discuss the full SDR reform impact evaluation (“effectiveness evaluation”), and then discuss the phase 1 sub-study. Then, we discuss the implementation science component of the study.

#### Full policy evaluation

This study will use a prospective, observational stepped wedge design. Kakamega County is planning to implement a phased rollout of SDR by sub-county, in three phases. Kakamega has 12 sub-counties: the reform will be implemented first (starting in 2022) in a group of 3 sub-counties. After a period of implementation in these “phase 1'' sub-counties, a second set of 4 sub-counties will implement the reform. After another period of implementation in these phase 2 sub-counties, a final set of 5 sub-counties will implement the reform (Fig. 2). This phased approach parallels the structure of a stepped wedge trial in that delivery and post-delivery outcomes for mothers and newborns can be compared within each group of sub-counties that implement SDR in the same implementation phase before and after the roll-out, as well as across counties in the same phase of rollout. Analytically, the analysis is also similar to that of a stepped wedge cluster randomized trial; the difference is that the order in which the clusters are exposed to treatment was decided not via randomization, but was decided by Kakamega County policymakers.

**Fig. 2 Fig2:**
[figure not shown]
Phases of Service Delivery Redesign implementation by sub-county in Kakamega County (Source: authors)

While noting the planned three phase design, we also have included an adaptive element to the evaluation study, due to the complex nature of the intervention: SDR is a multi-element, health systems intervention, requiring significant investment in infrastructure, human resources, and equipment. Furthermore, much of the investment is being executed using the county's public budget (in addition to contributions from the Gates Foundation). Given the public component of SDR spending and implementation through public sector institutions, the research team cannot fully anticipate the timing of the various elements of the stepped wedge design. Therefore in this trial we specify a secondary, interim design which leverages the first phase of SDR, described further below.

#### First phase interim evaluation

Embedded within the planned stepped wedge design is a difference-in-difference interim study design with the intervention occurring in phase 1 sub-counties (equivalent to the first “step'' or wedge in the planned stepped wedge sequence). This multi-stage design will enable the research team to evaluate interim results of the reform after phase 1. The design will also enable a full evaluation to be conducted even in the event that only one phase of the policy is implemented. In the event that the reform is only implemented in phase 1 subcounties, the research team will conduct an interim study after phase 1 implementation is completed, while also conducting a difference-in-difference study comparing outcomes in phase 1 subcounties to phases 2 and 3 subcounties over the full two year evaluation period.

### Participants

The research team has begun to enroll study participants from a sample of 72 facilities which provide ANC across all 12 sub-counties of Kakamega (enrollment started in February 2022) (Fig. 3). The selected facilities were stratified by sub-county and randomly selected proportional to volume of antenatal care visits, excluding facilities located within Kakamega Town (defined as three most densely populated wards in the vicinity of Kakamega Town). Sampled facilities were divided evenly between those in the three Phase 1 intervention sub-counties (36 facilities) and the other nine sub-counties (36 facilities). All private facilities were excluded, as the main SDR intervention components are not planned to take place in these facilities. Finally, facilities with the extremely low ANC volumes (< 6 new ANC clients per month) were excluded from the sample. These represent the lowest quartile of facilities by ANC volume in the county.

**Fig. 3 Fig3:**
[figure not shown]
Participant flow diagram

In each sampled facility, survey firm staff working with the research team seeks to enroll all pregnant women who present for antenatal care over a two year period (6 months of baseline and 18 months of implementation).^1^ Based on administrative data from 2021, we estimate that this sampling strategy will yield a sample of 59,753 mothers across the 72 facilities over two years. Approximately 98 percent of pregnant women in Kakamega County receive at least one ANC visit (National Bureau of Statistics et al. 2015). The approximate annual number of births in Kakamega County is 61,442, so over the two years of data collection approximately half of all pregnant women will be enrolled in the study. Any woman who reports that she intends to give birth outside at Kakamega County at the time of enrollment will be excluded. In addition, women who state upon enrollment that they have already made firm plans to deliver at a referral facility due to complications or previous caesarean sections will be excluded. Finally, all pregnant women below 15 years of age will also be excluded.

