### Data

The data collection strategy is informed by the SDR theory of change (Fig. 1), which has multiple pathways. According to the reform logic, in sub-countries where SDR has been implemented, pregnant women will change their care-seeking behavior by shifting their place of delivery from home or primary care clinics to delivery hub hospitals. The extent of this shift in care-seeking behavior will be measured by the main survey of enrolled pregnant women, hereafter referred to as the *pregnancy registry*. A second component of the theory of change is that delivery hubs, having been upgraded with better equipment, infrastructure, and staff, will deliver high quality intrapartum, postpartum, and newborn care. For the subset of women and newborns with life-threatening conditions (obstructed labor, sepsis, postpartum hemorrhage, low birthweight, birth asphyxia), timely and appropriate treatment will save lives, resulting in less maternal and newborn mortality and morbidity. We will measure both elements of this theory of change. Place of delivery and ultimate health outcomes will be measured through the pregnancy registry. Quality of care provided will be measured through facility and provider surveys, direct observations of deliveries, and women’s reports of quality from a subset of the main survey.

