To determine the appropriate number of facilities to sample, we calculated the power varying the number of facilities sampled from the treated and control sub-counties. We generated 1,000 simulated datasets followed the planned sampling design by first stratifying by sub-county and then sampling facilities with probability proportional to the number of antenatal care visits in 2021. Over the full study (following the stepped wedge design in which all sub-counties ultimately receive the SDR reform), we determined that we would have 89% power to detect a 12.5% reduction in composite outcome (a drop from 0.0406 at baseline to 0.0355) for 72 facilities, roughly corresponding to 60,000 births. To optimize power in the difference-in-difference Phase 1 study, we determined that equal allocation of 36 facilities in Phase 1 sub-counties and 36 facilities in Phase 2 and 3 sub-counties (18 facilities in Phase 2 and 18 facilities in Phase 3 sub-counties) would result in 86% power to detect a 30% reduction in composite outcome (with 72% power to detect a 25% reduction). For our secondary outcome of satisfaction, we determined that 2,000 women from the longitudinal study sample would result in > 80% power to detect a 0.15-standard deviation increase for both evaluation designs.

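### Excluding women with firm referral-facility plans makes enrolment depend on an intention that SDR may change, so it can bias the effect in a direction and by an amount the protocol does not determine

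*Protocol article*

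**What the plan says.** Under Participants, the protocol article excludes "women who state upon enrollment that they have already made firm plans to deliver at a referral facility due to complications" or previous caesarean sections. Enrolment at antenatal care runs for two years, "6 months of baseline and 18 months of implementation", and is expected to "yield a sample of 59,753 mothers across the 72 facilities over two years".

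The intervention section says that, once hubs are upgraded, "women are now expected to deliver at designated delivery hub hospitals". The message goes out through media campaigns, public meetings and "direct communication from health workers to antenatal care (ANC) clients". The Data section makes the behavioural step explicit: "pregnant women will change their care-seeking behavior by shifting their place of delivery from home or primary care clinics to delivery hub hospitals".

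Under Analysis, exposure follows sub-county of residence. Eq. (1) has a treatment term and a sub-county random intercept. The listed covariates are education, age, parity, transport time to the nearest hub, season and perceived pregnancy risk. Previous caesarean and diagnosed complications are not listed, although the Pregnancy registry section says antenatal complications are recorded at enrolment.

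**The concern.** The exclusion rests on a stated plan, not on a characteristic fixed before exposure. In sub-county periods where SDR is live, the plan may already reflect the policy. A woman with a complication or previous caesarean has the qualifying reason in hand. If SDR makes her more likely to say she has settled on a hospital birth, more such women are turned away after rollout than before, and the enrolled cohort becomes lower-risk through selection alone.

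Assigning exposure by residence is meant to keep choice of delivery place out of the comparison; this criterion lets it back in at enrolment. A change in exclusion that coincides with rollout loads onto the treatment term, and sub-county intercepts do not absorb it. Multiple imputation deals with outcomes missing among enrolled women, not with women never enrolled. Because the effect sought is modest ("a drop from 0.0406 at baseline to 0.0355"), a moderate shift in who is enrolled could matter.

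**Working it through.** **The plan's own figure.** The protocol states "89% power to detect a 12.5% reduction in composite outcome". Assume two-sided alpha 0.05, four six-month periods, and births split 50/25/25 across phases (from the 36/18/18 facilities). The exposed share is 0.50×0.75 + 0.25×0.50 + 0.25×0.25 = 0.5625, giving about 26,142 unexposed and 33,611 exposed births out of 59,753. Comparing 0.0406 with 0.0406×0.875 = 0.0355 by the two-proportion formula gives 89.6%, matching the stated 89%. A simulation of Eq. (1) with intercept SD 0.20 and equal sub-county volumes within phase gave 83.8% (500 runs, Monte Carlo SE 1.6 points). Actual facility volumes are not given, so that difference is not pursued here.

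**Selection model, with no true effect.** The protocol supplies only the overall risk, 0.0406. The rest is assumed: a share h of attenders is high-risk, with risk ratio R; a fraction e of them is excluded, e0 without SDR and e1 with it.

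- r_low = 0.0406 / (1 − h + hR); r_high = R × r_low
- Enrolled risk(e) = [(1 − h) r_low + h(1 − e) r_high] / (1 − he)
- Spurious relative reduction = 1 − risk(e1)/risk(e0)

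Worked case, h = 0.10, R = 3, exclusion 20% to 50%:

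- r_low = 0.0406/1.2 = 0.03383; r_high = 0.1015
- risk(0.2) = (0.03045 + 0.00812)/0.98 = 0.03936
- risk(0.5) = (0.03045 + 0.00508)/0.95 = 0.03739
- Reduction = 1 − 0.03739/0.03936 = 5.0%, or 40% of the 12.5% target

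| h, R | 20% to 30% | 20% to 50% | 30% to 10% |
|---|---|---|---|
| 5%, 1.5 | 0.2% | 0.7% | −0.5% |
| 10%, 2 | 0.9% | 2.7% | −1.7% |
| 10%, 3 | 1.6% | 5.0% | −3.3% |
| 15%, 3 | 2.2% | 6.8% | −4.4% |

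Positive entries are spurious reductions and negative entries spurious increases.

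**Effect on false conclusions.** In the Eq. (1) simulation with no true effect, a spurious reduction of 2.7% gave a significant benefit in about 10% of runs and one of 5% in about 20%. With no bias it was 3.8%, against a nominal 2.5% on that side.

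All these figures are unadjusted and apply the shift to every treated birth, so they lean high for any given set of inputs.

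**The case against.** A reader might infer that more high-risk women are in fact removed under SDR and that a spurious benefit follows. The document does not support that, for four reasons.

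- **A clinical reason is required.** A plan made only because of the SDR message does not exclude a woman.
- **Referral facility is not defined or equated with a delivery hub.** A high-risk woman planning to use her upgraded local hub, or citing the general policy as her reason, may stay enrolled. Exclusion could then fall and the sign reverse.
- **Timing weakens the pathway.** The plan must already exist at enrolment. Antenatal counselling is given in the same setting as enrolment, and communication is the last SDR component. Media and outreach could act earlier.
- **Adjustment is partial, not absent.** Parity and perceived risk are in the model. Adjustment need not recover unenrolled women; it has to balance risk among those enrolled, so the bias comes only from residual differences.

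All four stand, and they rule out a fixed direction or a single magnitude. They do not remove the problem. Perceived risk is an imperfect stand-in for previous caesarean and diagnosed complications, and may itself respond to SDR. Bias of unknown sign is still bias.

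There is also a fair objection to simply dropping the criterion. Enrolment began in February 2022, so women turned away at baseline are already lost. Admitting their counterparts only later is equivalent to exclusion going from 30% to 0%: with h = 10% and R = 3, risk moves from 0.03872 to 0.0406, a spurious increase of about 4.9%. The remedy has to avoid this.

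**Conclusion.** The concern holds in conditional form. The criterion selects on an intention that exposure may alter, it is applied after exposure begins in treated periods, and the stated model and covariates do not fully correct for a shift that coincides with rollout. Bias towards benefit is plausible, because high-risk women already meet the clinical limb and the policy promotes hospital birth, but the opposite sign is possible.

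Under the assumed inputs the distortion is between 2% and 55% of the 12.5% target when exclusion rises, and 4% to 36% of it in the other direction when exclusion falls. With a small high-risk group or a small shift it is negligible. A rise from 20% to 80% would give 1.5% to 14.4%, but nothing in the document points to so large a change. None of h, R, e0 or e1 is given, so these figures show what could happen and do not estimate the bias.

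**What to change.** 1. From now on, enrol, follow and flag women who state such plans instead of turning them away. Do not add them to the primary comparison against a baseline that lacks them.
2. Pre-specify an analysis of the composite restricted, in every period and sub-county, to women with neither complications recorded at enrolment nor a previous caesarean. These women cannot meet the exclusion's clinical limb, so the criterion cannot alter who is in this group. Require the primary result to be read together with it. Complications are already collected; previous caesarean needs one added question, asked at follow-up for women already enrolled.
3. Add recorded complications and previous caesarean to the adjustment set.
4. Define referral facility in relation to delivery hubs, and report the number excluded or flagged for stated plans by sub-county and period. Those counts would show whether exclusion moved with rollout, and in which direction.

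The cost is a small change to the enrolment and follow-up forms, some extra follow-up, and a narrower population with slightly less precision in the restricted analysis. Because women turned away cannot be recovered later, the change is worth more the sooner it is made.
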